#### Sensitivity Analyses

Sensitivity analysis and per-protocol analysis includes study subjects who meet certain criteria. For sensitivity, additional analysis of outcomes as stated above will include only subjects who completed follow-up at the primary 12 month endpoint. Because the SMS intervention protocol requires active participation of study subjects to respond and thus conduct the intervention as fully intended, per-protocol analyses will also be performed. Study participants in the intervention arm who respond to the weekly SMS's with an SMS back (active response) at least 80% of the time with the 48 hour time frame will be considered highly protocol-adherent; those who respond 50% to 80% of the time will be considered moderately protocol-adherent; those who respond less than 50% will be considered poorly protocol-adherent; and those that respond less than 20% will be considered least protocol-adherent. Subjects who are randomized to the SMS intervention but never respond with a return SMS, for whatever reason, will be considered as never responding and not included in the sensitivity analysis. We will also perform a sensitivity analysis to assess the impact of potential clustering of patients cared for by the same clinic.

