#### Sub-group analyses

Because a large clinical trial on this type of intervention has never been done before, we are interested in the interventions effect on various subgroups and the effect of multiple covariates on treatment outcomes. Subgroups of particular interests and potential covariates proposed are outlined in Table 2. Treatment arms will be compared with respect to potential covariates using continuous and categorical univariate analyses.

**Table 2 T2:** List of subgroups and potential covariates

**Subgroups of interest**	**Potential covariates**
Urban vs. rural	Age
By clinic	Gender
Female vs. male	Distance from clinic
Phone ownership (owned vs. shared)	Income level
Occupational designation	Cost to attend clinic
Level of education	Level of literacy
Usual mode of transportation used	Baseline quality of life
	HIV staging
	Level of disclosure of status
	Crossover into intervention

HAART = highly active antiretroviral therapy.

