#### Statistical methods

The intervention arm (SMS) will be compared against the control (SOC) for all primary analysis. We will use chi-squared test for binary outcomes, and T-test for continuous outcomes. For subgroup analyses, we will use regression methods with appropriate interaction terms (respective subgroup × treatment group). Multivariable analyses will be based on logistic regression (See Table 2) for binary outcomes and linear regression for continuous outcomes. We will examine the residual to assess model assumptions and goodness-of-fit. For timed endpoints such as mortality we will use the Kaplan-Meier survival analysis followed by multivariable Cox proportional hazards model for adjusting for baseline variables. We will calculate Relative Risk (RR) and RR Reductions (RRR) with corresponding 95% confidence intervals to compare dichotomous variables, and difference in means will be used for additional analysis of continuous variables. P-values will be reported to four decimal places with p-values less than 0.001 reported as p < 0.001. Up-to-date versions of SAS (Cary, NC) and SPSS (Chicago, IL) will be used to conduct analyses. For all tests, we will use 2-sided p-values with alpha = < 0.05 level of significance. We will use the Bonferroni method to appropriately adjust the overall level of significance for multiple primary outcomes, and secondary outcomes.

To assess the impact of potential clustering for patients cared by the same clinic, we will use generalized estimating equations [GEE] (ref) assuming an exchangeable correlation structure. Table 3 provides a summary of methods of analysis for each variable. Professional academic statisticians ([name]) blinded to study groups will conduct all analyses.

**Table 3 T3:** Variables, Measures and Methods of Analysis

**Variable/Outcome**	**Hypothesis**	**Outcome Measure**	**Methods of Analysis**
1) **Primary**	Intervention improved outcome from baseline to 6 months		
			
a) Adherence at 12 months		Percent adherence in previous 30 days >95% [binary]	Chi-squared test
			
b) Suppression of HIV viral load at 12 months		Viral load ≤400 copies/ml [binary]	Chi-squared test

2) **Secondary** Adherence percentage at 12 months	improvement occurred	Adherence % (>95%) [binary]	Chi-squared test

HIV viral load at 12 months	improvement occurred	Viral load (copies)	T-test

Immune reconstitution (change in CD4 T cell count from baseline)	improvement occurred	Cd4 T-cells/mm^3 ^(continuous)	T-test

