Time to virological failure	Improvement occurred	Virological failure after successful suppression	Kaplan-Meier survival analysis

Weight gain [lbs] and BMI	improvement occurred	Change in weight (lbs) and BMI [continuous]	T-test

Occurrence of opportunistic infections (OIs)	improvement occurred	Presence of AIDS defining opportunistic infection [binary]	Chi-squared test

Time to reporting of adverse drug events (ADEs)	improvement occurred	Presence of drug-related adverse event [time to event]	Kaplan-Meier survival analysis

Deaths (all cause)	improvement occurred	All-cause mortality [binary]	Chi-squared test and Kaplan-Meier survival analysis

SF-12	improvement occurred	Quality pf life questionnaire [continuous]	T-test

Satisfaction with care provided	improvement occurred	Questionnaire [continuous]	T-test

Level of disclosure of HIV status	improvement occurred	Disclosed to a family member [binary]	Chi-squared test

Impression of stigma	improvement occurred	Questionnaire [continuous]	T-test

Family dyamics	improvement occurred	Questionnaire [continuous]	T-test

Employment attendance	improvement occurred	Questionnaire [continuous]	T-test

Household member school attendance	improvement occurred	Questionnaire [continuous]	T-test

Cell phones lost/stolen	improvement occurred	Presence of cellphone [binary]	Poisson regression

Stopped taking HAART	improvement occurred	Self-report [binary]	Chi-squared test

Required active tracing for 12 month follow-up	improvement occurred	Field officers [binary]	Chi-squared test

3) **Subgroup Analyses:**			Regression methods with appropriate interaction term
Urban vs. rural	Distance affects adherence		
Female vs. male	Sex affects adherence		
Phone ownership (owned vs. shared)	Ownership affects adherence		
Level of education	Low education affects adherence		

4) **Sensitivity Analyses:**	improvement occurred	All outcomes	
a) Per protocol analysis			a) Chi-squared/T-test test
b) Adjusting for baseline covariates			b) Multivariable regression
c) clustering among individuals within a clinic			c) GEE

IMPORTANT REMARKS:

• The GEE[11] is a technique that allows to specify the correlation structure between patients within a hospital and this approach produces unbiased estimates under the assumption that missing observations will be missing at random. An amended approach of weighted GEE will be employed if missingness is found not to be at random.[12]

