### Ethics

The study is being conducted in accordance with the Helsinki declaration and established guideline for research on human subjects. The study protocol was approved by the University of Manitoba and Kenyatta National Hospital ethics review boards. All participants provide written consent. This study does not have a Data and Safety Monitoring Board. We do not have a code-breaking procedure for randomization as the study is unblinded, except for analysis. All protocol amendments will be approved first by the study primary investigators ([name]). The investigators have no competing interests. We will not provide post-trial care using SMS until approval from the ART funding body. All study results will be publicly available.

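### The blinding claim covers all analyses, but the per-protocol analysis uses an SMS reply rate that exists only in the intervention arm, so it cannot be run blind

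*Protocol article*

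**What the plan says.** Statistical methods states that professional academic statisticians "blinded to study groups will conduct all analyses", with no exception. Ethics confirms that nothing else in the trial is blinded: "We do not have a code-breaking procedure for randomization as the study is unblinded, except for analysis".

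Sensitivity Analyses says that "per-protocol analyses will also be performed", and item 4 of Table 3 lists "a) Per protocol analysis" against all outcomes. The top class is defined as "Study participants in the intervention arm who respond to the weekly SMS's with an SMS back (active response) at least 80% of the time", with a 48-hour limit. Lower classes are cut at 50% and 20%. Patients randomized to SMS who never send a reply are left out.

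The Control section says that controls are not sent the weekly messages. Data collection places the messages and replies in a weekly study log. A similar log of phone contacts is kept for controls.

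Table 2 lists "Crossover into intervention" among the potential covariates.

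**The concern.** A blind that covers every analysis requires that no analysis use information revealing the arm. The reply rate is such information. Statisticians who hold it know which code is SMS, so the stated property fails for at least one planned analysis.

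What is at stake is the judgement the plan leaves to the statisticians:

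- which of the potential covariates in Table 2 enter the multivariable models;
- whether missing data are judged not to be at random, which switches GEE to weighted GEE;
- how residuals and goodness of fit are read;
- how the multiple-imputation models are built;
- which subgroups are carried forward, since Table 2 names seven and Table 3 only four.

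Analyst blinding protects choices of this kind. If the reply data arrive first, the choices are made with the arms known. A report that repeated the blinding statement as it stands would also be inaccurate for the per-protocol results.

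**Working it through.** The point rests on no figure in the plan, so there is nothing to reproduce. The check sets the statements side by side.

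**1. Scope of the claim.** Statistical methods covers every analysis. Ethics limits the trial's blinding to the analysis stage. Together they say that the trial is open except for the statisticians, and that the statisticians are blind throughout.

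**2. What the per-protocol analysis needs.** It needs a reply rate for each SMS patient and a rule that removes never-responders. Both are written for patients randomized to SMS. No counterpart is given for controls.

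**3. Can a control have a value?** No. Without a weekly message there is no denominator for a reply rate. The control log records other phone contacts, so the reply fields unblind, not the existence of a log.

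**4. Does A/B coding protect the blind?** No. The reply rate can be filled under one code (target 267) and is empty under the other (target 267; 267 + 267 = 534). If the empty cells were set to zero, one non-zero value would still name the SMS code. If the statisticians received only a ready-made inclusion flag, every never-responder exclusion would fall under one code, so a single exclusion would name it.

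**5. Which analyses need the reply rate?**

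| Analysis | Needs reply rate? | Room for analyst choice |
|---|---|---|
| Two primary intention-to-treat tests | No | Little: fixed cut-offs, chi-squared test, missing counted as failure |
| Secondary intention-to-treat outcomes | No | Some: imputation models for data not directly related to adherence |
| Adjusted models | No | Yes: choice of covariates, model fit |
| GEE for clustering by clinic | No | Some: exchangeable structure is fixed, the switch to weighted GEE is not |
| Subgroup interactions | No | Some: Tables 2 and 3 list different sets |
| Per-protocol | Yes | Cannot be blind |

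So the blind can be kept for every row except the last, provided that the reply data come after the decisions in the other rows.

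**6. Crossover.** With coded arms, one patient recorded as having crossed into the intervention would name the control code. The variable is only a potential covariate, however. Table 3 describes the adjusted analysis as one for baseline covariates, and crossover occurs after baseline. If nobody crosses over, the variable reveals nothing. It is supporting evidence at most.

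**The case against.** The strongest reply is that the order of data release and the separation of analysts belong in a statistical analysis plan, which is not shown. The Analysis plan section also says that sensitivity and per-protocol work is done separately, which fits intention-to-treat first and per-protocol later. This stands as far as it goes: the article does not show that the reply data will reach the statisticians early, and its silence on order is no fault. But the point does not rest on that silence. The article makes an unqualified statement that its own per-protocol definition rules out. A staged analysis plan would still conflict with the word all.

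A second reply is that the primary comparison is hardly touched. That is correct, as the table in the working shows.

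A reader might infer that analyst blinding is the last safeguard in an open-label trial with a self-reported primary outcome. The document does not support this. Bias in self-report arises when the data are collected, and blinding the statistician does not remove it. The plan has other protections: a laboratory viral load with a fixed threshold as the other primary outcome, sealed opaque envelopes, and missing primary outcomes counted as failures.

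A reader might also infer that crossover alone identifies every patient. It does not, for the reasons in step 6.

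**Conclusion.** The blinding statement is too broad: the per-protocol analysis, planned for all outcomes, cannot be done by statisticians blind to group. Identification is complete once the reply rate is merged with coded arms. This assumes only that the variable is supplied as defined and that at least one SMS patient replies.

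The effect on any estimate cannot be computed from the document. It depends on whether the reply data arrive before modelling decisions are fixed, and on what those decisions would be. Exposure is small for the two primary tests. It is real but conditional for the adjusted, GEE, imputed and subgroup analyses. A reader might conclude that the trial's only blind is already broken, or that the primary result is compromised; the text supports neither. This is a correction worth making because it costs almost nothing, not a threat to the main comparison.

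**What to change.** Limit the sentence in Statistical methods to the intention-to-treat analyses, and give the phrase in Ethics the same limit. Then work in two steps:

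1. Give the statisticians arms coded A and B, without SMS-reply or crossover variables. Run the primary, secondary, adjusted, subgroup and clustering analyses on the intention-to-treat basis. Freeze the covariate and missing-data decisions.
2. Only then release the reply and crossover variables. Run the per-protocol analysis, and any analysis that uses crossover, and report both as unblinded.

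The cost is a change of wording and a data-release order. It needs no extra patients, data or staff. The downside is that the per-protocol results are openly labelled unblinded, which they are in any case.

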#### Primary outcomes

The first primary outcome is patient adherence to HAART at twelve months. (See Appendix) This is assessed by self-report using a standard questionnaire of the number of pills missed in the last 30 days and calculating percent adherence based on the expected number of doses taken. Percent adherence will be analyzed as a continuous variable and dichotomous variable. Subjects are considered either 'adherent' or 'non-adherent' using an optimal adherence cut off of > 95% of medications taken as directed.[1] Adherence is assessed at each follow-up visit and 'ever-non-adherent' will be our dichotomous outcome. The twelve month scheduled follow-up (defined, allowing for non-exact timing of clinic attendance, as follow-up up to 15 months if patients not present at 12 months) is the primary analysis. The six month assessment will allow for evaluating trends but is not the primary outcome.

The second primary outcome is suppression of plasma HIV RNA load at twelve months after initiating ART. If patients are adherent to HAART regimens, absorb the drugs normally, and if their virus is not resistant to the HAART drugs in the regimen, then plasma HIV load should be suppressed to below detectable levels (≤400 copies per ml) by six months and remain suppressed thereafter. Due to variability in when patients show up for scheduled appointments, we accept follow-up on or after 20 weeks as the six month outcome visit. Analysis of 'suppressed' (≤400 copies/ml) versus 'failure' to suppress (>400 copies/ml) at twelve months as a dichotomous variable is the primary analysis. However, decrease in plasma HIV load copies from baseline to twelve month follow-up will also be analyzed as the difference in a continuous variable from baseline to twelve months.

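### Continuous viral load is tested on raw copies, a scale that can lose most of the power, and the main tests for CD4, weight/BMI and SF-12 leave out the baseline value

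*Protocol article*

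**What the plan says.** The Statistical methods section sets one rule for all outcomes: "We will use chi-squared test for binary outcomes, and T-test for continuous outcomes". Table 3 applies it. HIV viral load at 12 months has the outcome measure "Viral load (copies" and the method t-test. The Primary outcomes section adds a second continuous analysis: "decrease in plasma HIV load copies from baseline to twelve month follow-up will also be analyzed as the difference in a continuous variable". No log scale, rank test or rule for values at the assay limit is named. The same section says that under effective treatment "plasma HIV load should be suppressed to below detectable levels (≤400 copies per ml) by six months", so many 12-month values are expected at or below that limit. For the co-primary it states that suppression versus failure "at twelve months as a dichotomous variable is the primary analysis".

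Three other continuous outcomes in Table 3 matter here, all with a t-test:
- "Immune reconstitution (change in CD4 T cell count from baseline"
- "Change in weight (lbs) and BMI [continuous"
- SF-12, entered as "Quality pf life questionnaire [continuous" and not described as a change.

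Baseline adjustment does appear. Statistical methods plans linear regression for continuous outcomes in the multivariable analyses, and Table 3 item 4b lists adjustment for baseline covariates as a sensitivity analysis covering all outcomes. Table 2 names the potential covariates. Baseline quality of life is among them; baseline CD4, weight and viral load are not. Residuals are to be examined, with no stated consequence.

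**The concern.** A t-test compares means. At 12 months the plan expects many patients at or below 400 copies/ml, while the failures may span several orders of magnitude. The arm mean in copies is then set by a few very high values, and its standard error is large. The raw change from baseline is worse, because untreated baseline values are larger and more variable than follow-up values, so their spread swamps any arm difference. A reader who sees a flat continuous result beside a positive suppression result could take the two as conflicting when the first simply had no power.

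For CD4, weight/BMI and SF-12, the patient's own baseline value is usually the strongest predictor of follow-up. Leaving it out of the main test gives up precision at no saving, on outcomes that also face the planned Bonferroni adjustment.

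**Working it through.** **The plan's own figure.** The article states no power or precision for any continuous outcome. Its one sample-size result, 247 per arm, concerns binary adherence at 75% vs 85%. I take from it only the arm size and, as an assumption, the same two rates for suppression, since no suppression rate is given.

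**Viral load: one case by hand.** Assumptions: suppressed values set to 400; failures with log10 copies of mean 4 and SD 0.7; failure 25% vs 15%; 247 per arm; two-sided alpha 0.05.

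- *Raw copies.* On the natural-log scale the SD is 0.7 × 2.3026 = 1.612. The mean among failures is 10⁴ × exp(1.612²/2) ≈ 36,655. The arm difference is 0.10 × (36,655 − 400) ≈ 3,626. Arm SDs are about 66,510 and 51,710, so SE = √((66,510² + 51,710²)/247) ≈ 5,360. Ratio 0.68; normal-approximation power about 10%.
- *log10.* log10(400) = 2.602. Difference 0.10 × (4 − 2.602) = 0.140. Arm variance is p × 0.49 + p(1−p) × 1.398², which is 0.489 at p = 0.25 and 0.323 at p = 0.15. SE = √(0.812/247) = 0.057. Ratio 2.44; power about 68%.
- *Raw change.* Assume baseline log10 of mean 5 and SD 0.7, independent of follow-up. The baseline SD is then about 1.29 million copies. SE ≈ 116,400 against the same 3,626. Ratio 0.03; power about 5%, the same as the test level.

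**Viral load: simulation** (4,000 replicates, two-sided alpha 0.05; values capped at 10⁷ in the 247-per-arm runs).

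| Assumed scenario | Raw t-test | log10 t-test | Raw change | log10 change |
|---|---|---|---|---|
| 75% vs 85% suppressed; failures' log10 mean 3.5–4.5, SD 0.7–1.0; 247 per arm | 8–18% | 53–73% | 4–6% | 22–49% |
| 50/60, 60/70, 70/80% suppressed; failures' log10 mean 4.3, SD 0.9; 240 per arm | 9, 10, 12% | 44, 49, 59% | – | – |
| Equal suppression (75%); failures shift by 0.5 log10, SD 0.8 | 41% | 44% | 5% | 27% |
| 75% vs 85% and failures shift by 0.3 log10 | 44% | 91% | 5% | 66% |
| No effect (75% in both arms) | 2.6% | 5.2% | 4.7% | 5.1% |

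Further runs under varied distributions with a 10-point gain gave 5–14% on raw copies and 34–68% on log10. The chi-squared test on suppression has about 80% power in the first row. With an illustrative Bonferroni divisor of 17 (the 16 rows of Table 1 plus retention), at 75% vs 85% and failures of mean 4 and SD 1.0, raw power is 0.2% and log10 power 22%.

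**Baseline adjustment.** Take equal variance σ² at both times and correlation r, which the article does not give. The arm comparison has variance proportional to 2(1−r)σ² for a change score, σ² for follow-up only, and (1−r²)σ² with baseline as covariate. The cut is therefore 1 − (1−r²)/(2(1−r)) = (1−r)/2 against change, and r² against follow-up only.

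| r | Variance cut vs change | SE cut vs change | Variance cut vs follow-up only |
|---|---|---|---|
| 0.3 | 35% | 19% | 9% |
| 0.5 | 25% | 13% | 25% |
| 0.7 | 15% | 8% | 49% |
| 0.8 | 10% | 5% | 64% |
| 0.9 | 5% | 2.5% | 81% |

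**The case against.** The strongest reply is that the clinically used form of viral load is already a co-primary. It is binary at 400 copies/ml, so neither skew nor the limit touches it. That stands. Nor is there a false-positive risk: with no effect the raw t-test rejects 2.6% of the time at a nominal 5%.

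Second, the size depends on the scenario. A reader might infer that a raw t-test always discards most of the power. The documents do not support that: they give no viral-load distribution, and if only the level among failures moves, raw and log10 are close at 12 months (41% vs 44%). However, the article's own hypothesis is better suppression, which is the case where the loss is large, and the raw change score stays near 5% in every scenario.

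Third, a reader might infer that baseline is never adjusted for. That is wrong: item 4b covers all outcomes and Table 2 lists baseline quality of life. What remains is that this is a sensitivity analysis and that baseline CD4, weight and viral load are not named. An unadjusted change score is also unbiased under randomisation, so this part concerns efficiency and is not an error. Nor does one percentage fit all three outcomes. SF-12 is not stated to be a change score, and for weight, where r may well be 0.8 or more, the gain is 10% of variance or less.

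Fourth, an article may leave transformations to an analysis plan, and the word copies might only name a unit. But the article fixes both measure and test, and defines the second analysis as a difference in copies. Examining residuals without a stated consequence would leave any switch of scale to be made after seeing the data.

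**Conclusion.** The point holds in two parts of unequal weight. The heavier one is viral load. As written, both continuous analyses use a poor scale: if the effect runs through the proportion suppressed, power is roughly 5–18% at 12 months and about 5% for raw change, against about 35–70% for 12-month log10 values. These figures rest on assumed suppression rates and distributions and on alpha 0.05. The loss is in power, on a secondary outcome.

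The lighter one is baseline adjustment: a free gain in the main tests for CD4, weight/BMI and SF-12. Its size follows from r, which is assumed: a 35% to 5% cut in variance against a change score for r from 0.3 to 0.9 (19% to 2.5% in standard error), and r² for a follow-up-only SF-12 score.

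**What to change.** In Table 3 and the Primary outcomes section, analyse continuous viral load as log10 copies/ml. Fix the rule for values at or below 400 in advance: set them to the limit, with censored regression as a sensitivity check, since that model leans on a distributional assumption when many values are censored.

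In Table 3, make linear regression on arm, the outcome's own baseline value and clinic the main analysis for CD4, weight/BMI and SF-12. Keep unadjusted change as descriptive.

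The cost is wording; no extra patients are needed, and the CD4 and weight changes already require a baseline value. The small downside is that a log10 difference is less direct to read than a difference in mean copies.

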**Methods and Design:**

A multi-site randomized controlled open-label trial. A central randomization centre provided opaque envelopes to allocate treatments. Patients initiating ART at three comprehensive care clinics in Kenya will be randomized to receive either a structured weekly SMS ('short message system' or text message) slogan (the intervention) or current standard of care support mechanisms alone (the control). Our hypothesis is that using a structured mobile phone protocol to keep in touch with patients will improve adherence to ART and other patient outcomes. Participants are evaluated at baseline, and then at six and twelve months after initiating ART. The care providers keep a weekly study log of all phone based communications with study participants.

Primary outcomes are self-reported adherence to ART and suppression of HIV viral load at twelve months scheduled follow-up. Secondary outcomes are improvements in health, quality of life, social and economic factors, and retention on ART. Primary analysis is by 'intention-to-treat'. Sensitivity analysis will be used to assess per-protocol effects. Analysis of covariates will be undertaken to determine factors that contribute or deter from expected and determined outcomes.

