#### Secondary outcomes

The potential benefits of the intervention are quite broad, so multiple secondary outcomes are of interest and were selected through academic collaboration. The secondary outcomes fall under the categories of health, quality of life, social factors, and economic indicators (see Table 1). The primary purpose of taking antiretroviral medications for HIV infection is to maintain or restore health in someone who is HIV infected. Several other factors that contribute to a subject's prosperity or overall well-being may be affected directly (by way of enhanced support mechanisms associated with the intervention), or indirectly (through improvements in health related to HAART effect). We therefore feel it is important to assess each of these outcomes independently.

**Table 1 T1:** Secondary Outcome Measures

**Secondary outcome measures (6 months and 12 months post initiation of HAART)**	**Type**
*Health outcomes*	
Self-reported adherence as a percentage	Binary
Suppressed HIV viral load (in copies)	Continuous
Immune reconstitution (change in CD4 T cell count from baseline)	
Time to virological failure	Continuous
Weight gain [lbs] and BMI	Time-to-event
Occurrence of opportunistic infections (OIs)	Continuous
Time to reporting of adverse drug events (ADEs)	Binary
Deaths (all cause)	Time-to-event
*Quality of life (QOL)*	Time-to-event
SF-12	
Satisfaction with care provided	Continuous
*Social factors*	Continuous
Level of disclosure of HIV status	
Impression of stigma	Binary
Family dyamics	Continuous
*Economic factors*	Continuous
Employment attendance	
Household member school attendance	Continuous
Cell phones lost/stolen	Continuous

HAART = highly active antiretroviral therapy, SF-12 = short form 12 adapted for regional application in Kiswahili.

In addition, we hypothesize that the intervention will lead to improved retention on ART.[5] Because participants are actively traced for twelve month follow-up visits, we will use composite retention outcomes. We define 'retained' as someone who followed-up on their scheduled visit without being traced and is still taking ART versus 'unretained' which includes subjects who stopped taking ART before their twelve month visit, who are lost to follow-up, or required active tracing after missing their scheduled twelve month appointment. We will report each element of the composite endpoints.[6]

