### Analysis plan

#### Analysis of primary and secondary outcomes

The trial will be reported according to the CONSORT standards for reporting randomized trials. We will use intention to treat (ITT) principles for primary outcome analysis and conduct additional sensitivity and 'per protocol' analysis separately as outlined below. Intention to treat implies all subjects randomized are considered in outcomes as per randomization. In this analysis we will impute missing outcome data as treatment failures. For adherence assessment, missing data at 12 months will be considered as 'non-adherent'; for viral suppression analysis, missing data at 12 months will be considered as virologic failures. We will use multiple imputation for imputing missing data that are not directly related to adherence. It is considered the gold standard for handling missing data because it leads to unbiased estimates of the effect and standard errors compared to single imputation methods.[8]

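### Time to virological failure counts only failure after suppression, so patients who never suppress cannot have the event and the between-arm comparison can mask or reverse a real benefit

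*Protocol article*

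**What the plan says.** Table 1 (Secondary outcomes) lists "Time to virological failure" without a definition. Table 3 (Statistical methods) supplies one: the outcome measure is "Virological failure after successful suppression", the hypothesis is that improvement occurred, and the method is "Kaplan-Meier survival analysis". The text of the same section adds a Cox model for timed endpoints. The article does not give this outcome's time origin or risk set, or say how a patient who never suppresses is handled.

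Elsewhere, failure has a wider meaning. For the second primary outcome, suppression "versus 'failure' to suppress (>400 copies/ml) at twelve months as a dichotomous variable is the primary analysis" (Primary outcomes), and "for viral suppression analysis, missing data at 12 months will be considered as virologic failures" (Analysis of primary and secondary outcomes).

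On timing, the Abstract states: "Participants are evaluated at baseline, and then at six and twelve months after initiating ART". In adherent patients without resistance or absorption problems, "plasma HIV load should be suppressed to below detectable levels", and this is expected "by six months and remain suppressed thereafter" (Primary outcomes). The Primary objectives hypothesise that the SMS intervention improves adherence and, through it, suppression.

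**The concern.** The event can occur only in patients who first suppress. First suppression is a post-randomisation result that the intervention is expected to influence. The article leaves two readings of the Table 3 row open, and both have a problem:

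- **Never-suppressed patients are left out, or the clock starts at suppression.** The arms are then compared within a subgroup selected after randomisation on something treatment may change.
- **All randomised patients stay in from ART start.** The randomised comparison is kept, but a patient whose viral load never falls to 400 copies/ml is treated as free of virological failure.

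Under either reading the same patient is a failure in the primary outcome and cannot fail in a secondary outcome of almost the same name. A trial in which SMS raises suppression could then report a secondary virological result of no effect or apparent harm, and readers would take the two results as conflicting evidence.

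The timing information is also thin. With evaluations at baseline, six and twelve months, rebound after suppression at month 6 can be seen essentially only at the twelve-month visit.

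**Working it through.** The article states no event rate, hazard ratio or power for this outcome, so there is no figure to reproduce. The arithmetic below illustrates the effect of the definition.

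**Inputs**

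- Patients per arm: 267 (Sample size).
- Proportion suppressed at month 6, s: 75% control and 85% SMS. This is an assumption. The figures are the adherence rates from the Sample size section, used as stand-ins.
- Proportion of those suppressed who are above 400 copies/ml at month 12, f: 10% in both arms. This is an assumption.
- Follow-up complete to month 12. A patient first suppressed at month 12 has no later visit at which to rebound, so also has no event.

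**Risk of the event by month 12**

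- A, suppressed patients only: f
- B, all randomised, unsuppressed patients event-free: s × f
- C, all randomised, non-suppression at month 6 counted as failure: (1 − s) + s × f

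**Central case**

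- Patients who could carry no event: 267 × 0.25 = about 67 control; 267 × 0.15 = about 40 SMS.
- A: 10.0% v 10.0%, risk ratio (SMS/control) 1.00.
- B: 0.75 × 0.10 = 7.5% v 0.85 × 0.10 = 8.5%, ratio 1.13.
- C: 0.25 + 0.075 = 32.5% v 0.15 + 0.085 = 23.5%, ratio 0.72.

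**Varying the assumptions**

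| Suppression, control v SMS | Rebound, control v SMS | A | B | C |
|---|---|---|---|---|
| 75% v 85% | 10% v 10% | 1.00 | 1.13 | 0.72 |
| 75% v 85% | 5% v 5% | 1.00 | 1.13 | 0.67 |
| 65% v 75% | 10% v 10% | 1.00 | 1.15 | 0.78 |
| 75% v 85% | 10% v 12% | 1.20 | 1.36 | 0.78 |
| 75% v 85% | 10% v 15% | 1.50 | 1.70 | 0.85 |
| 75% v 85% | 10% v 8% | 0.80 | 0.91 | 0.67 |
| 75% v 85% | 10% v 6% | 0.60 | 0.68 | 0.62 |

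For the last two rows:

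- SMS rebound 8%: B = 0.85 × 0.08 / 0.075 = 0.068 / 0.075 = 0.91; C = (0.15 + 0.068) / 0.325 = 0.67.
- SMS rebound 6%: B = 0.051 / 0.075 = 0.68; C = (0.15 + 0.051) / 0.325 = 0.62.

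B equals 1 when SMS rebound is 0.10 × 0.75 / 0.85 = 8.8%, a relative reduction of about 12%. With equal or higher rebound under SMS, the Table 3 definition hides or reverses the benefit seen in C. With rebound sufficiently lower under SMS, A and B also favour SMS, and in the last row A slightly exceeds the benefit in C.

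**Timing.** The Primary outcomes section accepts the six-month visit from 20 weeks onward and the twelve-month visit up to 15 months. Data collection aims for samples at the study visit or within two weeks of it. Observed rebound dates would therefore spread over those windows, but they would mark when patients attended, not when viral load rose.

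**The case against.** The best defence is that durability of suppression is a legitimate question in its own right, and that never-suppressed patients are already counted in the second primary outcome. Risk set and censoring rules are also commonly left to a full protocol or analysis plan that is not shown here. This is one of many secondary outcomes, the article plans a Bonferroni adjustment for them, and the explicit intention-to-treat commitment is for the primary outcomes. All of that limits the weight of the point. It does not remove it: the event definition is stated, it is tested between arms as an SMS improvement, and no choice of risk set lets a never-suppressed patient have the event.

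Three stronger readings are tempting, and the article supports none of them:

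- **The randomised comparison is lost.** That is true only if never-suppressed patients are excluded or the clock starts at suppression. If everyone is followed from ART start, the comparison is as randomised, and the fault is that the endpoint measures rebound only.
- **The outcome will show SMS as harmful.** One can construct this. With suppression of 65% v 75%, rebound of 8% in those who would suppress in either arm and 30% in the extra 10 points, the risk among suppressed SMS patients is (0.052 + 0.030) / 0.75 = 10.9%, a ratio of 1.37 to control. Taking 5–10% and 20–40% for the two rebound rates gives 1.13 to 1.93. But those ratios follow from assuming that SMS does nothing for rebound and that the extra suppressors rebound more. A 27% relative reduction in rebound under SMS cancels the 1.37 (1 / 1.37 = 0.73).
- **The Kaplan-Meier curve has a single step.** The visit windows spread the steps out. The supportable statement is that their timing mainly reflects attendance.

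**Conclusion.** The point holds for a secondary outcome. As defined in Table 3, time to virological failure cannot register patients who never suppress, and it conflicts with the meaning of failure in the primary viral-load outcome. Whichever way those patients are handled, the comparison can mask or reverse a real virological benefit. In the central illustration a ratio of 0.72 becomes 1.00 or 1.13.

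That size rests on assumed suppression and rebound rates. The article gives neither, and both size and direction change with them, so the figures show a possible distortion and do not predict harm. The primary suppression outcome counts never-suppressed patients correctly, and its conclusion does not depend on this row.

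**What to change.** For the between-arm test, redefine the Table 3 row to include all randomised patients from ART start, with failure as viral load above 400 copies/ml at the six-month visit or later. A patient not suppressed at month 6 then fails in the first interval. Analyse the two visit intervals with a discrete-time or interval-censored model in place of Kaplan-Meier on attendance dates. Keep failure after suppression as a separate item, label it as rebound among patients who suppressed, and report it descriptively by arm.

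The cost is one reworded row, a matching label in Table 1 and a different model, using data already collected at the trial's own threshold. The small downside is overlap with the primary suppression outcome. A patient above 400 copies/ml at month 6 but suppressed at month 12 would be a failure here and a success there. The plan should say so.
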